### Trial design

See Fig. 1 for the study flow chart. This is a pilot and feasibility randomised controlled trial, which comprises a 12-week intervention period followed by a 12-week follow-up period. Randomisation will ensure a 1:1 allocation ratio of participants to either Cognitive Remediation Therapy (CRT) in addition to Treatment-As-Usual (*n* = 30) or TAU alone (*n* = 30) for the intervention period. Measures will assess the outcomes before (baseline; week 0), after (week 13) the intervention period, and after the follow-up period (week 25). Two self-report symptom measures of depression and mania will be completed by all participants at weeks 1, 4, 8 and 12 during the intervention period to monitor wellbeing.

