#### CRT intervention

CRT will be delivered over the course of a 12-week period, flexibly utilising a combination of formats (i.e., face-to-face, telephone, drop-in sessions and individual practice), amounting to approximately 30–40 hours of CRT. Face-to-face sessions (up to 1 hour long) will be held at least once per week, but participants will be encouraged to attend up to three sessions per week if feasible; an alternative arrangement of twice-weekly telephone sessions (in addition to one face-to-face session) will be offered. Additionally, all individuals will be provided unlimited access to use the program in their own time, for practising independently as they wish, with an option to receive reminder text-messages that can be sent to participants up to twice per week. This intervention aims are tailored to individual needs, using a format beneficial for themselves specifically. Where possible, and only with the participants’ agreement at each session, therapy meetings will be video-recorded or auditory-only recorded; this will assist with ensuring therapist fidelity and optimising the intervention for future use. CRT is considered a safe therapy, unlikely to have an impact on risky behaviours, and the participants should not be experiencing symptoms during the trial. Though we perceive this not to be a high-risk study, the participants are considered a vulnerable population, and a small risk exists that they will not engage positively with, or more importantly, will have a negative emotional reaction to the intervention (e.g. frustration may be experienced upon failure to complete a particular task). Despite existing evidence indicating that people find CRT helpful and acceptable, we will ensure that CRT therapists are comprehensively trained and prepared to manage such situations (using supportive and solution-focused approaches). Effort will be put into avoiding such circumstances by following standardised protocols which researchers will be trained in for adverse situations. We emphasise that the intervention is delivered using positive methods and has reliably elicited positive feedback from patients during previous trials. CRT therapists will be psychologists (to post-graduate-level study at minimum), who have received specific training from experts in the intervention, on CRT and the CIRCuiTs program specifically. They receive ongoing supervision from experienced CRT practitioners. Processes are in place to deal with any safety issues that include ongoing participant monitoring throughout the intervention period; completion of self-report symptom measures on a monthly basis, and prompts from a researcher to safeguard completion and scoring. In any instances where scores exceed the standardised cut-offs for depression or mania, individuals will receive a call from a researcher (or a therapist if concerns persist). If necessary, a therapist or clinician and participants will discuss and agree whether there is a need for trial withdrawal. Additional concerns about safety and wellbeing will be conveyed to the participant’s contact healthcare professional. A copy of the consent form alongside a letter of notification and information sheet is sent to nominated healthcare professional for all participants. Trial participation (and whether CRT is being undertaken) is to be recorded on patient’s health records as the trial affects clinical care and may be important for treatment-related decisions. A data management plan (in adherence with the Research Governance Framework) has been developed to ensure protocols for quality assured monitoring and safety are maintained during the trial. Data monitoring support is also accessible through the trial steering committee and trial specific working manual.

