### Statistics

Analyses will be carried out by the trial statistician. The main purpose of the statistical analyses is to estimate trial and intervention feasibility parameters. Thus, we will use largely descriptive statistics with inferential statistics used to generate respective confidence intervals and effect sizes. The analyses can be split into three aims: 1) estimation of parameters that evaluate trial feasibility (recruitment rates, randomisation rates and attrition rates), to meet objective 4; 2) estimation of parameters that measure intervention feasibility (adherence, treatment fidelity and patient satisfaction) in accordance with objective 3; and 3) estimates of intervention effect sizes (mean differences and standard deviations) in terms of potential primary outcomes of future trials or variables that are targeted by the therapy (putative mediators of future treatment effects), addressing objectives 1 and 2. All statistical analyses will adopt the intention-to-treat (ITT) principle and will be conducted after data collection has been completed.

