#### Estimates for effect sizes for CRT versus TAU (objectives 1 and 2)

To assess improvement in cognitive and functioning domains, estimates of treatment effect sizes will be obtained using linear mixed models. These analyses will provide the treatment effect estimate on each outcome at 13 and 25 weeks. The linear mixed model will contain post-treatment measures of the outcome at the two follow-up time points, i.e. 13 and 25 weeks as the dependent variables with fixed effects of trial arm, baseline measure of outcome, time and a time point by trial arm interaction to allow treatment effects to differ at 13 and 25 weeks. Baseline measures of the primary outcomes are included as they are potential predictors of future outcome and thus should help us to gain precision for effect estimates of interest. A random effect for participant will be entered in to the model to account for correlations between the two repeated measures per participant. In addition, to account for the correlation of level-1 residuals across time, an exchangeable residual covariance structure will be included in the model. We will also consider changes in cognitive variables as mediators of improvements in functional outcomes (FAST). The aim here is to derive an effect size and inferential statistics will not be reported.

With respect to missing data, linear mixed models will be estimated using maximum likelihood (ML). Such an approach provides valid inferences under the assumption that the missing data mechanism is ignorable (or missing at random, MAR). Here, this means that explanatory variables included in the model can predict missingness as can earlier observed values of the outcome. We will include baseline predictors of drop-out as explanatory variables in the linear mixed model to make the MAR assumption more realistic. However, given the small dataset the number of explanatory variables to be included will be necessarily small. Finally, Sensitivity analysis will be used to assess the robustness of the conclusions to missing outcome data in which missing values will be imputed according to various plausible scenarios, e.g. participants with missing data showing no improvement in cognitive outcomes.

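### Interim mood scores can lead to trial withdrawal but are left out of the mixed model, so the stated missing-at-random reasoning does not cover that drop-out

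*Protocol article*

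**What the plan says.** **Monitoring and withdrawal.** Under Trial design, "Two self-report symptom measures of depression and mania will be completed by all participants at weeks 1, 4, 8 and 12"; Table 1 identifies these as the IDS and ASRM. Under CRT intervention, "In any instances where scores exceed the standardised cut-offs for depression or mania, individuals will receive a call from a researcher", with a therapist calling if concerns persist. The next step is discretionary: "If necessary, a therapist or clinician and participants will discuss and agree whether there is a need for trial withdrawal".

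**Model.** Under Estimates for effect sizes for CRT versus TAU, "The linear mixed model will contain post-treatment measures of the outcome at the two follow-up time points, i.e. 13 and 25 weeks". The fixed effects are arm, baseline outcome, time and time by arm, with a participant random effect. Predictors of drop-out may be added, but only baseline ones and only a few, because the dataset is small.

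**Missing data.** The model is fitted by maximum likelihood under an assumed ignorable mechanism, explained thus: "this means that explanatory variables included in the model can predict missingness as can earlier observed values of the outcome". Sensitivity imputation under several scenarios is planned; the one example is "participants with missing data showing no improvement in cognitive outcomes".

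**Principle.** Under Statistics, "All statistical analyses will adopt the intention-to-treat (ITT) principle".

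**The concern.** The protocol describes a way out of the trial that starts from observed post-baseline data, and then rests its missing-data argument on a model containing none of those data. Someone who withdraws after a raised score at week 4, say, contributes nothing to the week 13 and 25 likelihood. The model in effect treats that person like participants in the same arm with the same baseline who stayed. If those who stayed had better mood, and mood bears on the outcome, the arm mean is too favourable.

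The outcomes most exposed are the mood and functioning measures of objective 2. When the IDS or ASRM is itself the outcome, its values at weeks 1 to 12 exist but are not among the dependent variables. The stake is the third statistical aim: effect sizes meant to inform a larger trial.

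**Working it through.** **No plan figure to reproduce.** The article gives no drop-out rate, SD or effect size. Every rate and effect below is an assumption; only the 30 per arm comes from the document.

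**Step 1: what the model conditions on.** For loss before week 13 it has arm, baseline outcome and baseline drop-out predictors. The variable that can start withdrawal, interim IDS/ASRM, is neither a covariate nor an earlier outcome value. Missingness is at random given the model only if interim mood carries no further information on the missing outcome. That is plausible to doubt for cognition and FAST, and hard to believe for mood outcomes.

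**Step 2: size of the bias in closed form.** Let p be the share exceeding a cut-off, w the share of those who withdraw, and d the amount by which an episode lowers the outcome, in SD.

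- Episode share among those remaining = p(1 − w)/(1 − pw)
- Bias of CRT minus TAU = d × (TAU share − CRT share)

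With w = 0.6 in CRT and 0.2 in TAU:

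| p | CRT share | TAU share | Difference | d = 0.5 | d = 1.5 |
|---|---|---|---|---|---|
| 0.2 | 0.08/0.88 = 0.091 | 0.16/0.96 = 0.167 | 0.076 | 0.04 | 0.11 |
| 0.3 | 0.12/0.82 = 0.146 | 0.24/0.94 = 0.255 | 0.109 | 0.05 | 0.16 |

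- Swapping the two withdrawal rates reverses the sign.
- Equal rates (0.8 and 0.8) give zero.
- The extreme of all against none gives 0.10-0.15 SD (d = 0.5) and 0.30-0.45 SD (d = 1.5).

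**Step 3: scale.** With 30 per arm and an assumed baseline-to-week-13 correlation of 0.7, the standard error is √(2/30) × √(1 − 0.7²) = 0.258 × 0.714 = 0.18 SD.

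**Step 4: large-sample simulation.** One million participants per scenario, true effect zero, 25% exceeding the cut-off when mood is unaffected by treatment. Rho is the partial correlation of interim mood with outcome. Entries are the bias of the week-13 contrast in SD.

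| Scenario (drop-out CRT vs TAU) | rho 0 | 0.2 | 0.4 | 0.6 |
|---|---|---|---|---|
| Same rule, no effect on mood (12.5% vs 12.5%) | 0 | 0 | 0 | 0 |
| Same rule, CRT improves mood by 0.5 SD (6% vs 12.5%) | 0 | −0.01 | −0.02 | −0.03 |
| 80% vs 20% of those exceeding withdraw (20% vs 5%) | 0 | +0.04 | +0.07 | +0.11 |
| 100% vs 0% (25% vs 0%) | 0 | +0.06 | +0.12 | +0.18 |

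Zero means within simulation noise. In the first row the contrast is sound, although the control-arm mean shifts by 0.02, 0.05 and 0.08 SD at rho 0.2, 0.4 and 0.6. Imputing within arm from baseline and interim mood brought the bias to at most 0.004 SD throughout.

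**Step 5: does the remedy work at 30 per arm?** One indicator of any cut-off exceedance, used as an auxiliary variable, removed the bias. Root mean squared error was 0.210 with it and 0.208 without for the 0.5 SD effect, and 0.259 against 0.274 for 1.5 SD. Eight interim scores imputed separately by arm did poorly in a separate check: bias fell only from 0.047 to 0.037, while root mean squared error rose from 0.207 to 0.223.

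**The case against.** The article puts missing at random forward as an assumption, adds baseline predictors to make it more realistic, and backs it with sensitivity scenarios. Nothing there is false or self-contradictory. This stands, and it limits the point to a gap in the justification.

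A reader might infer that the assumption simply fails for the drop-out the protocol creates. The documents do not support that:

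- A raised score prompts a call; withdrawal is discussed only if needed, and the article does not say that withdrawal ends outcome assessment.
- Whether interim mood predicts the outcome beyond arm and baseline is not established.
- Even if it does, the contrast is unbiased when both arms share the same withdrawal process and mood course.

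A reader might also infer that TAU participants only self-report and so are bound to be withdrawn less often. Prompts and calls are not restricted to the CRT arm, and adverse events are monitored at every time point (Other measures). CRT participants do have at least weekly face-to-face sessions, and the Discussion hopes CRT may prevent mood symptoms, so a difference between arms is possible. The 60/20 split has no source.

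Nor do the documents show that the no-improvement scenario makes matters worse. With retest gains in both arms it would favour CRT only if TAU lost more participants, the opposite of the pattern in Step 2. With CRT losing more, it pulls against that bias: it left 0.018 SD in one check with an assumed 0.3 SD retest gain. The article fixes no single-value fill-in or variance method, so a charge of understated standard errors is not available. What remains is that the only example is confined to cognitive outcomes and not tied to mood-related loss.

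Finally, drop-out reasons and non-attendance, at assessments and by therapy session, will be described. That goes part of the way to separating stopping therapy from missing follow-up.

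**Conclusion.** The point holds as a gap: a withdrawal route that can start from interim IDS/ASRM scores lies outside the information on which the model's missing-at-random reasoning rests. Its consequence is conditional and its direction uncertain. In the 60/20 illustration the bias is 0.04-0.05 SD for an episode effect of 0.5 SD, roughly a quarter of the standard error, and 0.11-0.16 SD for 1.5 SD, approaching the standard error. Under a common process it is about zero. These sizes rest on assumed exceedance rates, withdrawal rates and episode effects. In a pilot whose main purpose is feasibility and whose effect sizes are for estimation, this is something to consider, not a flaw that invalidates the analysis.

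**What to change.** **CRT intervention section.** State separately that a participant stops CRT and that a participant withdraws from follow-up, and record each. Keep inviting everyone to the week 13 and 25 assessments unless they decline. No clinical decision changes.

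**Effect-size section.** Add a multiple-imputation analysis, or a joint likelihood, that includes arm, baseline outcome and one or two summaries of interim mood (for example any cut-off exceedance, or worst IDS/ASRM score), and then fit the same mixed model. The summaries serve as auxiliary variables only. They are post-randomisation and could absorb treatment effect if entered as covariates in the effect model.

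**Sensitivity analysis.** Add one delta-adjusted scenario, applied by arm, for mood-related withdrawal.

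**Cost.** The mood scores are already collected, so the cost is a form field, some extra analysis work and slightly wider intervals. Imputing separately by arm from all eight interim scores (two scales at four weeks) is not advised at 30 per arm.

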#### Economic analyses

Service use measured with the Client Service Receipt Inventory will be combined with appropriate unit costs [46]). The costs of the intervention, which will be based on the resources required to deliver it (staff time and overheads) and activity levels, will be added to these. The EQ5D will be used to derive quality-adjusted life years. These will be combined with the costs and comparisons made between the two groups. Uncertainty will be addressed using cost-effectiveness planes derived though bootstrapped resamples.

## Discussion

CRT has the potential to increase cognitive function and for improvements to translate to quality of everyday life and social and occupational functioning, as well as possibly to prevent the onset of mood symptoms. Our findings should indicate whether a partly computerised, 12-week course of cognitive remediation therapy can improve cognition above treatment-as-usual.

### Strengths

This study has been designed and is being conducted in compliance with the principles of the Declaration of Helsinki (1996), the principles of Good Clinical Practice (GCP) and in accordance with all applicable regulatory requirements including but not limited to the Research Governance Framework and the Mental Capacity Act (2005). These actions will maximise validity, participant safety and scientific integrity as well as reduce bias. Additionally during the planning stages we sought review of the scientific quality of the study from a service user panel (NIHR/MHRN’s FAST-R - Feasibility and Support to Timely recruitment for Research - service) and informally by experienced academics and clinicians prior to two stringent peer review processes for funding application. The study was judged to be well-designed by a strong team, and to be worthwhile in terms of putative future implications. Trial Steering Committee monitoring (which includes all study investigators, individuals independent from the study team and service user representatives), regular and experienced supervision for therapists, and ongoing support and training for those undertaking research assessments will ensure that quality is maximally maintained throughout the trial.

### Limitations

Participants will be recruited via a number of routes, and although this may increase the representativeness of people with bipolar type I disorder, it may also increase heterogeneity of our findings. The flexibility of the CRT intervention (in terms of different modes of provision and aspects focused on) may also increase heterogeneity. Due to participant burden and resources, we are not able to account for all potential confounders. In addition, as we are not excluding participants based on cognitive deficits, it is possible that some of our participants might have high functioning and therefore not show improvements with CRT (something important to be addressed in future studies). The sample size for this pilot trial is relatively small to detect differences of the domains being measured and provides a comparison of CRT with treatment as usual care alone. The results will inform a more comprehensive RCT comparing a CRT intervention with an active placebo condition, to establish the effects of CRT for a group of people diagnosed with bipolar disorder controlling for non-therapeutic but potentially important factors (e.g. cognitive task-specific improvements and time engagements).

This publication of our protocol aims to maximise reproducibility and transparency of this pilot trial, which is investigating the effects of CRT for people with bipolar disorder; our findings will indicate whether this accessible program provides benefits to this population over treatment-as-usual, which would represent a vital advance in psychological care for asymptomatic bipolar disorder.

## Trial status

The trial is ongoing. Recruitment commenced in February 2016.

## Abbreviations

C4C, Consent for Contact—SlaM service to facilitate patient recruitment into research; CIRCuiTs, Computerised program for cognitive Remediation Therapy; CRF, clinical research facility; CRiB, Cognitive Remediation in Bipolar study; CRT, cognitive remediation therapy; DSM-IV, Diagnostic & Statistical Manual for Mental Disorders version IV; OPTIMA, Specialist clinical service in SLaM for affective disorders; RCT, randomised control trial; SLaM, South London & Maudsley NHS Foundation Trust; TAU, treatment as usual
